## Methods: data collection, management, and analysis

### Data collection plan

After giving informed consent, the patient will receive a unique identifier, after which members of the research team will extract all necessary clinical parameters from the electronic health records (EHRs, HiX) into an electronic Case Report Form (eCRF) the UMCU endorsed system Castor EDC. Castor EDC is a browser-based, metadata-driven EDC software solution and workflow methodology for building and managing online databases. The eCRF contains data items as specified in this research protocol. Modification of the eCRF will be made only if deemed necessary and in accordance with an amendment to the research protocol. Access to the eCRF is password protected and specific roles are assigned (e.g., study coordinator, investigator, monitor). The assessors are specialized in the field of otology and are therefore trained to interpret the results of the various outcome measures (CBCT scans, speech performance tests, impedance values). Participant retention will be promoted by efficient schedule strategies, namely inviting participants for follow-up appointments on the same days as the clinical rehabilitation consults. The study participants will receive a separate invitation for each follow-up appointment, shortly before.

### Data management

Data handling and protection are conducted according to the ISO 27001-compliant processes and ICH-GCP and applicable regulations. Confidentiality will be maintained at all times and participant information will not be disclosed to third parties. After giving informed consent, the patient will receive a unique identifier. All generated (meta)data will be stored in a secure research folder structure for access control. Only researchers directly involved in the study and the monitor of the study are allowed to access the key-linking table to enable patient re-identification. The paper data files and informed consent will be stored in a locked cabin in a locked room. Only research members directly involved in this study and the monitor of the study will get access to all of the collected research data. When required, authorized personnel of the study can access the pseudonymized source data for intermediate analysis or business intelligence reports.

### Statistical analysis

To assess whether continuous variables are normally distributed, histograms and Q-Q plots will be computed. Continues data will be expressed as mean ± standard deviation (SD) when normally distributed, and as median ± interquartile range (IQR) when skewed. Number of cases and percentages will be presented as categorical variables. A *p*-value <0.05 is considered statistically significant. All analyses will be conducted according to the intention-to-treat principle.

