**Methods and analysis:**

This single-blind randomized controlled trial will recruit a total of 112 primary cochlear implantation adult patients, eligible for implantation according to the current standard of practice. Randomization will be performed by an electronic data capture system Castor EDC, with participants block randomized to either bony recess or standard subperiosteal tight pocket in a 1:1 ratio, stratified by age. The primary outcome of this study is the R/S device migration rate; secondary outcomes include patient-experienced burden using the validated COMPASS questionnaire, electrode migration rate, electrode impedance values, speech perception scores, correlation between R/S migration, electrode array migration and patient complaints, assessment of complication rates, and validation of an implant position measurement method. Data will be collected at baseline, 1 week, 4 weeks, 8 weeks, 3 months, and 12 months after surgery. All data analyses will be conducted according to the intention-to-treat principle.

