#### Trial design

This is a single-blind, non-inferiority randomized controlled trial, with two study arms (Fig. 1). Patients will be randomly allocated into equally sized groups: group A and group B (allocation ratio 1:1). Patients in group A will be operated with the bony recess technique, and patients in group B will be operated with the subperiosteal tight pocket technique. Inclusion in the study will have no consequence for the model or brand chosen by the patient, as is currently standard practice.

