### Interventions: modifications

Modifying the allocated intervention would require a revision surgery where the cochlear implant would be removed. Revision surgery is potentially harmful for the patient; therefore, it will only be performed in rare cases such as device failure, wound infection, or persisting pain.

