### Randomization and blinding

Patients will be randomly assigned to one of the two study groups with 56 patients allocated in each group. Randomization takes place in the UMC Utrecht-endorsed electronic data capture system Castor EDC. (https://www.castoredc.com/). After giving informed consent, patients will be randomized with an allocation ratio of 1:1 and variable block sizes, with stratification for age (18–50 years, >50 years). Stratification is applied in both study groups. This is a single-blind study, meaning that only participants are blinded for the treatment allocation. The randomization will be done before surgery and patients will not be informed about the allocation. The research team is not blinded. The outcome data will be blindly analyzed. Blinding of the data will be performed by the electronic Case Report Form system used (see section “Data collection plan”). In the event that a revision surgery is necessary for removal or repositioning of the CI, unblinding is permitted. A member of the research team will inform the subject of the allocation.

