#### Statistical analysis secondary objectives

COMPASS questionnaire scores between intervention and control at 3 and 12 months after cochlear implantation will be calculated using the unpaired *t*-test (or the Mann-Whitney *U* test).

Statistical analysis of electrode migration data will be compared in a number of cases and percentages. To calculate any association between electrode migration of ≥ 1 mm and R/S device migration, and between electrode migration and a decrease in speech performance tests, Pearson’s correlation test or a Spearman rank correlation test will be performed. Electrode impedance values will be compared between the groups with the unpaired *t*-test (or the Mann-Whitney *U* test). CVC word score tests (with and without noise) will be compared between the groups with the unpaired *t*-test. Within-group comparisons will be calculated with differences of mean values. A clinically relevant speech performance decrease is a speech performance test score decrease of ≥ 7% when scoring between 30 and 80%, and ≥ 5% when the patients’ scores < 30 or > 80% on the speech performance test, a definition based on clinical experts. Incidence and degree of complications will be reported by means of frequencies.

Participants who withdraw from the study prematurely will be considered lost and will be replaced. Reasons for withdrawal or premature termination will be documented. Potential missing data will be handled using multiple imputation. Complete case analyses will be performed as a sensitivity analysis. All analyses will be performed on an intention-to-treat basis.

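### All analyses of this non-inferiority trial are restricted to intention-to-treat, and no planned analysis covers patients operated with the technique they were not allocated

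*Protocol article*

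**What the plan says.** The Trial design section is explicit about the hypothesis: "This is a single-blind, non-inferiority randomized controlled trial, with two study arms". The Sample size section sets the margin at 1.0 mm.

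The analysis principle is stated three times, each time for every analysis:

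- Abstract, Methods and analysis: "All data analyses will be conducted according to the intention-to-treat principle".
- Statistical analysis: "All analyses will be conducted according to the intention-to-treat principle".
- Statistical analysis secondary objectives: "All analyses will be performed on an intention-to-treat basis".

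One sensitivity analysis is named, in the same paragraph as multiple imputation: "Complete case analyses will be performed as a sensitivity analysis". No per-protocol or as-received analysis appears in the text shown.

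Two passages bear on whether patients receive what they were allocated. Randomization and blinding says: "The randomization will be done before surgery and patients will not be informed about the allocation". Interventions: modifications says: "Modifying the allocated intervention would require a revision surgery where the cochlear implant would be removed". It adds that such surgery will be done only in rare cases.

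**The concern.** Intention-to-treat keeps each patient in the allocated arm whatever operation was done. If some patients receive the other technique, the arms become more alike and the estimated difference moves towards zero. In a superiority trial that works against the trial's claim. In a non-inferiority trial with a real excess of migration, it works in favour of the claim.

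The planned complete-case analysis does not help, because it drops patients with missing data and leaves those who received the other technique where they were allocated.

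At stake is a conclusion about safety. The Discussion itself says that the safety of the pocket technique has not been proven with certainty. A reader of a positive result would want to know that it does not depend on patients who had the other operation.

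**Working it through.** **Inputs from the Sample size section:** margin 1.0 mm, SD 2.0 mm, 51 per arm, 80% power, significance level 0.05 with no sidedness given.

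**The plan's own figure.** With a true difference of zero, n per arm = 2 × SD² × (z for alpha + z for power)² / margin².

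- One-sided 0.05: 2 × 4 × (1.645 + 0.842)² / 1² = 49.5, so 50. The exact noncentral-t calculation gives 51, the stated figure.
- One-sided 0.025: 2 × 4 × (1.960 + 0.842)² / 1² = 62.8, so 63 (64 by t).

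The stated 51 therefore implies a one-sided 5% level. Because the article does not say so, both levels are carried below.

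**Assumptions for the dilution.**

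- The true excess in the pocket arm, if everyone received the allocated technique, equals the margin, 1.0 mm.
- The net crossover c is the share of the pocket arm that receives the recess plus the share of the recess arm that receives the pocket.
- A patient who crosses over has the mean migration of the technique received, and the SD is unchanged.
- Non-inferiority is concluded when the upper confidence limit lies below 1.0 mm. The sample size calculation implies this test. The primary analysis section names only tests of a difference between groups.
- The values of c are assumed, since the documents give none.

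**Formulas.**

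- Standard error: SE = 2.0 × √(2/51) = 0.396 mm.
- Expected intention-to-treat difference: 1.0 × (1 − c).
- False non-inferiority rate: Φ(c × 1.0/SE − z for alpha).

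Worked example for c = 10% at one-sided 5%: 0.10/0.396 = 0.252; 0.252 − 1.645 = −1.392; Φ = 0.082.

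| Net crossover c | Patients, if all in one arm of 51 | Expected difference (mm) | False non-inferiority, one-sided 5% | One-sided 2.5% |
|---|---|---|---|---|
| 0% | 0 | 1.00 | 5.0% | 2.5% |
| 2% | 0.02 × 51 ≈ 1 | 0.98 | 5.5% | 2.8% |
| 5% | 0.05 × 51 ≈ 2.6 | 0.95 | 6.4% | 3.3% |
| 10% | 0.10 × 51 ≈ 5.1 | 0.90 | 8.2% | 4.4% |
| 20% | 0.20 × 51 ≈ 10.2 | 0.80 | 12.7% | 7.3% |

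With 56 analysed per arm instead of 51, the one-sided 5% figures for 2%, 5%, 10% and 20% are 5.6%, 6.5%, 8.4% and 13.2%, so the choice of n hardly matters.

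**The case against.** The strongest reply is that there may be almost nothing to dilute. The intervention is a single operation done by the surgeon, with no course of treatment for the patient to abandon. The article says that modifying the allocated technique would need revision surgery and calls that rare. At 2% net crossover, about one patient in an arm, the error rate moves by half a percentage point. This stands as a limit on the weight of the point. It does not settle it, because the revision passage concerns removal of an implant already in place and is silent on a different technique being used at the operation itself. A low rate in theatre is therefore also an inference.

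A second reply is that a per-protocol set breaks the randomized comparison and can be biased in either direction. That stands too. It is why such an analysis should support intention-to-treat and not displace it. It also argues against excluding revised patients. The Background lists pain, device failure and revision surgery among the possible consequences of migration, and the modifications section gives device failure and persisting pain as reasons for revision. Such an exclusion could remove the outcomes of interest.

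A third reply is that analysis sets belong in a statistical analysis plan. That has little force here. The article is not silent: it assigns all analyses to intention-to-treat, so a later plan that added another set would depart from its wording.

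Two stronger readings are tempting. A reader might infer that intention-to-treat is in itself the wrong choice for non-inferiority. The documents do not support that, since any bias exists only in proportion to departures from allocation. A reader might also infer, from the Background's remarks on dural exposure and cortex thickness, that surgeons will switch away from drilling in some patients. The article describes no such switch.

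**Conclusion.** The point holds in a conditional form. The article fixes intention-to-treat for every analysis of a declared non-inferiority trial, and its one sensitivity analysis does not address the technique received. If some patients are operated with the other technique, the stated analysis may be anti-conservative.

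At one-sided 5%, the increase over the nominal rate runs from 0.5 percentage points at 2% net crossover to 7.7 points (12.7 − 5.0) at 20%. At one-sided 2.5% it runs from 0.3 to 4.8 points (7.3 − 2.5). These figures rest on a true excess exactly at the margin, on the stated SD and sample size, and on crossover rates that are assumed throughout. The 20% row would need about ten of 51 patients in an arm to have the other operation, and nothing in the documents predicts that.

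This is a missing low-cost safeguard, not a demonstrated threat to the trial's conclusion.

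A related matter deserves attention when the sets are defined: "Participants who withdraw from the study prematurely will be considered lost and will be replaced". Replacing withdrawn participants fits poorly with intention-to-treat and leaves the analysed population unclear.

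**What to change.** - Keep intention-to-treat as the primary analysis.
- Record, for every patient, the fixation technique actually used at surgery, and report the number of departures by arm.
- Pre-specify a per-protocol analysis limited to patients who received the allocated technique. Use the same model and the same missing-data handling as the primary analysis, so that the two results differ only by population. Make no exclusion for revision.
- Report the confidence interval for the difference in migration against the 1.0 mm margin in both sets, and state the one-sided level.
- Describe a non-inferiority claim as robust only if the two results are consistent. If they diverge, report the divergence and discuss the departures behind it.
- Amend the three statements that assign all analyses to intention-to-treat, so that the added analysis does not contradict them.

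The cost is one data item per patient and one extra analysis. Sample size, visits and surgery do not change. The per-protocol set will be somewhat smaller and is not fully protected by randomization, so it supports the intention-to-treat result and does not replace it. If no one crosses over, the two analyses coincide and nothing is lost.

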#### Statistical analysis primary objective

The main outcome is R/S device migration calculated by analyzing 3D reconstructions of the R/S device, acquired by CBCT scans at baseline and during follow-up. Migration will be reported in millimeters and angle degrees (continuous variables) between the intervention group and the control group at baseline and 3 and 12 months after implantation. Differences between the intervention and control group will be calculated using the unpaired *t*-test or the Mann-Whitney *U* test.

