#### Objectives

The primary objective of our study is to compare the migration rates of the two fixation techniques (bony recess vs. subperiosteal tight pocket) by analyzing 3D reconstructions of the R/S device, acquired by cone-beam computed tomography (CBCT) scans at baseline and at 3 and 12 months post-surgery. Secondary objectives are to investigate the difference between the two fixation techniques in patient-experienced burden using the validated COMPASS questionnaire, electrode array migration rate, and electrode impedance values. Other secondary objectives are to investigate the association of electrode impedance values with R/S device and electrode migration, and whether complaints of performance drop, vertigo, tinnitus, headache, or nonauditory stimulation are associated with electrode array migration and R/S device migration. We will also compare the complication rate of these surgical techniques, for major and minor complications. Finally, we will validate the measurement method technique with flexible tape measure for the assessment of migration of the R/S device [35].

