#### Primary outcome measure

The main outcome of this study is R/S device migration and will be calculated by analyzing 3D reconstructions of the R/S device, acquired by cone-beam CT (CBCT) scans at baseline and during follow-up and at 12 months. We consider migration either translational or rotational above 1.0 mm or 1° as clinically relevant. Any migration under these cut-offs is considered within the measurement error margin of the analysis (0.3 mm or degrees). These calculations will be carried out by using 3DMedX® (v1.2.24.1, 3D Lab Radboudumc, Nijmegen). R/S positions will be superimposed, compared, and analyzed based on the Iterative Closest Point (ICP) algorithm [36]. The 3D reconstructions of the R/S device at baseline and 12 months will be compared to calculate the primary outcome measure.

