### Sample size

This sample size calculation was based on the primary outcome, R/S migration after 12 months. Due to limited quality evidence on the migration rate for both techniques, an estimation of the migration rates cannot be based on literature; therefore, we base our assumptions on clinical expertise [34, 42, 43]. We consider a migration under 1.0 mm or 1° to be clinically irrelevant. Migration under these cut-off points is within the measurement error margin of the measurement technique of the CBCT scan analysis. A sample size of 51 per study arm reaches 80% power (*β* = 0.8) and a significance level (*α*) of 0.05 with a non-inferiority margin of 1.0 mm. Standard deviation is estimated at 2.0 mm based on the database of Maxwell et al. [43]. In order to cover for possible loss to follow-up estimated at a maximum of 10%, we will include 56 patients per study arm.

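### The primary outcome is named as a migration rate, but sample size, margin and primary analysis concern mean millimetres, and no between-arm comparison of the rate is planned

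*Protocol article*

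**What the plan says.** The protocol article describes the primary question in two ways.

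**As a rate.** The Abstract (Methods and analysis) states: "The primary outcome of this study is the R/S device migration rate". The Objectives section agrees: "The primary objective of our study is to compare the migration rates of the two fixation techniques". The Abstract's Background gives the same aim. The Primary outcome measure section supplies the event that a rate needs: "We consider migration either translational or rotational above 1.0 mm or 1° as clinically relevant".

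**As an amount.** The Statistical analysis primary objective section says "Migration will be reported in millimeters and angle degrees (continuous variables) between the intervention group and the control group", and then "Differences between the intervention and control group will be calculated using the unpaired *t*-test or the Mann-Whitney *U* test". The Sample size section works on the same scale: "A sample size of 51 per study arm reaches 80% power", with "a significance level (*α*) of 0.05 with a non-inferiority margin of 1.0 mm" and an SD of 2.0 mm. It assumes no migration rate for either arm and sets no margin on a rate. It also sets no margin in degrees.

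The design is stated as non-inferiority: "This is a single-blind, non-inferiority randomized controlled trial, with two study arms". The section on the primary analysis does not mention the margin.

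**The concern.** A rate of relevant migration and a mean displacement are different quantities. If most devices stay put and a minority move clearly, the mean spreads the movement of the few over the many. A difference in means below 1.0 mm can then go with a large difference in the share of patients whose device moved by more than 1.0 mm.

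The article uses 1.0 mm for both purposes. In the Primary outcome measure section it is the limit of relevance for one patient's device. In the Sample size section it is the tolerated difference between group means. The first does not justify the second.

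Two things are at stake. The pocket technique could be called non-inferior while the question in the Objectives is answered unfavourably, or not at all. And with two descriptions of the primary outcome in print, the choice between them could be made after the results are known.

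**Working it through.** **1. The plan's own figure.** Inputs from the Sample size section: margin 1.0 mm, SD 2.0 mm, power 80%, α 0.05 (sidedness not stated). Assume a true difference of 0.

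n per arm = 2 × SD² × (z₀.₉₅ + z₀.₈₀)² / margin² = 2 × 4 × (1.645 + 0.842)² / 1 ≈ 49.5, so 50. With the t distribution, 50 per arm gives 79.9% power and 51 gives 80.6%. The stated 51 is reproduced at one-sided 0.05. At one-sided 0.025 the formula gives 63 (64 with the t distribution), which does not match. The trial is therefore sized on a difference in mean mm.

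**2. What passes at the planned SD.** SE = 2.0 × √(2/51) = 0.396 mm. Non-inferiority at one-sided 5% requires an observed mean difference below 1.0 − 1.660 × 0.396 = 0.34 mm.

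**3. Mixture scenarios (assumptions, not figures from the article).** Unmoved devices read |N(0, 0.3)| mm, with mean 0.3 × √(2/π) = 0.239 mm. Migrated devices move a fixed distance m. Rates are 5% (bony recess) v 20% (pocket), 51 per arm, 20,000 simulated trials. Non-inferiority is declared when the upper one-sided 95% limit for the mean difference is below 1.0 mm.

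True mean difference = (0.20 − 0.05) × (m − 0.239).

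| Migrators move | Mean difference | Pooled SD | Declared non-inferior |
|---|---|---|---|
| 3 mm | 0.41 mm | about 0.9 mm | about 93% |
| 4 mm | 0.56 mm | about 1.2 mm | about 56% |
| 5 mm | 0.71 mm | about 1.5 mm | about 26% |

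Letting migrators vary around the same averages (SD 1.5, 2.0 and 2.5 mm) gives 84%, 50% and 25%.

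**4. The same mean differences at the planned SD.** With SD 2.0 mm, the chance is approximately Φ((0.34 − d)/0.396). For d = 0.41 mm this is about 43%; for d = 0.56 mm, about 29%.

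**5. Skewed displacement at SD 2.0 mm (assumed gamma or lognormal).** Means of 0.5 v 0.8 mm, a difference below the 0.34 mm limit in step 2, imply about 10% v 19% of devices above 1 mm. Means of 0.5 v 1.4 mm, a true difference of 0.9 mm and still inside the margin, imply about 10% v 40–42%. So the planned SD does not remove the mismatch.

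**6. What 51 per arm can say about a rate.** With 10% in both arms, the 95% half-width of the risk difference is 1.96 × √(2 × 0.1 × 0.9 / 51) = 0.116, about 12 points. The smallest rate margin with 80% power at one-sided 5% is (1.645 + 0.842) × √(2p(1 − p)/51): about 11, 15 and 20 points for p = 5%, 10% and 20%.

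**The case against.** The strongest reply is that *rate* is loose wording. The Primary outcome measure, Sample size and Statistical analysis primary objective sections all speak of R/S device migration, and the latter two work in mm or in mm and degrees. On that reading the operative sections largely agree, and the Abstract and Objectives need a change of label. This has force and is why the fix below keeps mm as primary. It does not remove the point: the article still disagrees with itself on its primary outcome, and it defines a cut-off that the primary analysis never uses.

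A second reply is that counts are provided for, or belong in an analysis plan not shown. The general Statistical analysis section does foresee case numbers and percentages for categorical data, so a descriptive count of migrators is possible. That is not a between-arm comparison of the declared primary outcome. The article does state its primary analysis, and it is for another variable.

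A third reply concerns size, and it stands. A reader might infer from the 93% figure that the trial would very probably pass a fourfold higher rate. The documents do not support that. The scenarios in step 3 have SDs of about 0.9 to 1.5 mm against the planned 2.0 mm, and the chance falls quickly as migrators move further. The simulation covers translation only. It also applies a margin test on means, which the analysis section does not spell out. Such skewed data might go to the Mann-Whitney test instead, which does not compare means.

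**Conclusion.** The contradiction is in the text and needs no simulation: the outcome and objective are a rate, the size and primary analysis are continuous, and the proportion above 1.0 mm or 1° is not compared between arms in any section shown. A several-fold higher rate of relevant migration could therefore be compatible with non-inferiority on the mean.

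The probability is assumption-dependent. For 5% v 20% it runs from about 93% to about 26% as migrators move 3 to 5 mm, and it is about 43% and 29% for mean differences of 0.41 and 0.56 mm at the planned SD. All of these assume 51 per arm and a one-sided 5% margin test on means. The trial is not powered for a claim about rates.

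It would go too far to say that a continuous primary endpoint is wrong in itself, or that the rate has to be primary. The documents show only that the two have not been reconciled.

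**What to change.** Make the objective, primary outcome, margin, sample size and primary analysis refer to one variable. Because the trial is sized on mm:

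- Name the primary endpoint as R/S displacement in mm from baseline to 12 months, and drop the rate as primary outcome from the Abstract and Objectives.
- State in the primary analysis section that non-inferiority is judged by a confidence limit for the difference in means against the 1.0 mm margin.
- Have the sponsor state the role of rotation. It is part of the cut-off and of the analysis, but no margin in degrees is given.
- Add, as a key secondary analysis, the proportion per arm above the cut-off (mm or degrees) at 12 months, with the risk difference and a 95% CI (for example Newcombe or Miettinen-Nurminen).
- State that conclusions about migration rates rest on that interval, for which the trial is not powered.

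If the sponsor prefers to keep the rate as primary, it needs a rate margin and a new sample size. Step 6 shows that 51 per arm supports only wide margins.

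The mm route costs some wording and one additional analysis of scans already planned, with no extra patients or scans. Its downside is a visibly wide interval for the rate.

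### The trial is designed and sized for non-inferiority with a 1.0 mm margin, but the stated primary analysis is a test of difference at p<0.05 that does not use the margin

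*Protocol article*

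**What the plan says.** The Trial design section of the protocol article states: "This is a single-blind, non-inferiority randomized controlled trial, with two study arms". The title says the same. The Sample size section gives the design figures: "A sample size of 51 per study arm reaches 80% power", at alpha 0.05, with "a non-inferiority margin of 1.0 mm". It adds: "Standard deviation is estimated at 2.0 mm".

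The section on the statistical analysis of the primary objective says that migration will be reported in millimetres and degrees, and then: "Differences between the intervention and control group will be calculated using the unpaired" t-test or the Mann-Whitney U test. The general Statistical analysis section supplies the only decision criterion, a p-"value <0.05 is considered statistically significant".

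The margin on the group difference appears only in the Sample size section. The 1.0 mm under Primary outcome measure is something else: a cut-off for calling an individual patient's migration clinically relevant.

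**The concern.** A non-inferiority trial has to reject the hypothesis that the new technique is worse by the margin or more. The stated tests, read in the ordinary way, address the hypothesis of no difference. When the two techniques perform alike, which is what the sponsor hopes to show, such a test usually returns a non-significant p-value. That is not evidence that an excess of 1.0 mm has been excluded.

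The article uses the same test wording for the COMPASS scores and impedance values under the secondary objectives. Nothing in the text marks the primary comparison as a different kind of question.

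The choice between tests adds to the problem. Migration analysed as a distance cannot be negative and may well be right-skewed, so the Mann-Whitney branch is plausible. As described, that test gives no mean difference in millimetres to set against 1.0 mm.

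At stake is the main conclusion of the trial: whether the drill-free technique holds the device well enough.

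**Working it through.** **Inputs.** Margin 1.0 mm, SD 2.0 mm, alpha 0.05 and 80% power, all from the Sample size section. Allocation is 1:1. The assumed true difference and the sidedness of the test are not stated; a difference of 0 is assumed, and both levels are tried.

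**Step 1: reproduce the plan's sample size.** Normal approximation per arm: n = 2 × SD² × (z for alpha + z for power)² / margin².

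- One-sided 0.05: 2 × 4 × (1.645 + 0.842)² / 1 = 49.5, so 50. The exact t-based calculation gives 51, with 80.6% power.
- One-sided 0.025: 2 × 4 × (1.960 + 0.842)² / 1 = 62.8, so 63. The t-based calculation gives 64. At 51 per arm the power is 70.6%.

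The stated 51 is therefore a margin-based calculation at one-sided 0.05 with a true difference of 0.

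**Step 2: what each rule requires at 51 per arm.** The standard error is 2.0 × √(2/51) = 0.396 mm, with 100 degrees of freedom.

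- Two-sided difference test: significant if the absolute observed difference exceeds 1.984 × 0.396 = 0.79 mm.
- Margin-based, one-sided 0.05: non-inferior if the observed difference is below 1.0 − 1.660 × 0.396 = 0.34 mm.
- Margin-based, one-sided 0.025: non-inferior if it is below 1.0 − 1.984 × 0.396 = 0.21 mm.

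**Step 3: how the rules behave (non-central t, normal data).**

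| True excess with the pocket (mm) | Difference test not significant | Non-inferior, one-sided 0.05 | Non-inferior, one-sided 0.025 |
|---|---|---|---|
| 0 | 95.0% | 80.6% | 70.6% |
| 0.5 | 76.0% | 34.8% | 23.9% |
| 1.0 | 29.4% | 5.0% | 2.5% |

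With no true difference, the difference test is significant in 100 − 95 = 5% of trials, and by symmetry half of these (2.5%) favour the pocket. The 80% power belongs to the margin-based test in the third column.

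The 29.4% in the last row is an error rate only if a non-significant result is read as non-inferiority. Under that reading, fewer patients make a pass easier: 35.0% at 45 per arm and 40.2% at 40 per arm.

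**Step 4: sensitivity to skew (illustration only; none of these inputs comes from the documents).** Suppose both arms have measured movement with mean 0.4 mm and SD 0.3 mm, and 10% of pocket devices shift a further 10 mm. The mean excess is then 0.10 × 10 = 1.0 mm, exactly the margin. At 51 per arm, simulation gives a non-significant Mann-Whitney result in about 85% of trials. An upper limit from an unequal-variance interval falls below the margin in about 10% of trials at one-sided 0.05 and 8 to 9% at one-sided 0.025. With a percentile bootstrap the figure is about 9 to 10%. The margin-based rule is much safer here, but its error exceeds the nominal level.

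**The case against.** The strongest defence is that the wording is incomplete rather than wrong. The sentence names a t-test without giving its null hypothesis, its sidedness or a rule for the conclusion. A t-test shifted by the margin is a standard non-inferiority analysis, and the sample size shows that someone had it in mind. A journal article condenses; the full protocol and any analysis plan are not shown, and a part of the article itself was not available for this check. This stands as a reason not to assume what the sponsor intended. It does not remove the point. The article does name the primary test and a significance rule, and together they describe a test of difference that does not match the stated design.

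Stronger readings are tempting, but the documents do not support them:

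- *The analysis could never establish non-inferiority.* A significant result favouring the pocket would imply it, and a t-test analysis also produces the mean difference and standard error needed for the comparison with the margin. What is missing is the decision rule.
- *The plan has a 29% false-positive rate.* That needs the rule that p≥0.05 means non-inferior, which the protocol nowhere states.
- *The Mann-Whitney test would miss most harmful patterns.* The 85% figure rests on an invented pattern of shifts. The Sample size section itself says that the literature cannot supply migration rates.
- *A margin-based test guarantees 5% error.* This holds for approximately normal data, not under the strong skew of Step 4.

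**Conclusion.** The point holds: the stated primary analysis does not match the design. The title, trial design and sample size set a non-inferiority question with a 1.0 mm margin, and the analysis sections give a test of difference at p<0.05 into which the margin does not enter.

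The firm part of the size is that, with no true difference, the stated test is significant 5% of the time, while the margin-based test that the sample size describes succeeds 80.6% of the time. The conditional part is the 29% against 5% at a true excess of 1.0 mm. It assumes SD 2.0 mm, 51 analysed per arm, approximate normality and a reading of non-significance that the protocol does not state.

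Because the rule decides the trial's main conclusion, it should be corrected before outcomes are compared between arms.

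**What to change.** In the section on the primary objective, replace the sentence on the test with a decision rule, for example: *Non-inferiority of the subperiosteal pocket is concluded if the upper confidence limit for the difference in mean migration in mm from baseline to 12 months (pocket minus recess) is below 1.0 mm.*

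Alongside it:

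- State the level. One-sided 0.05 reproduces 51 per arm with 80.6% power. One-sided 0.025 gives about 71% power at 51 per arm, and 80% would need 63 to 64.
- Use an unequal-variance or bootstrap interval for the mean difference, and note that under strong skew its error can exceed the nominal level (about 10% in the illustration above).
- Keep the Mann-Whitney test as supportive only.
- Report rotation in degrees separately, because the 1.0 mm margin does not apply to it.

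The cost is rewording. No new data are needed, and no more patients if one-sided 0.05 is kept. Choosing one-sided 0.025 means accepting the lower power or recruiting more.
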